## Abstract

**Purpose:**

To mitigate the risk of infection and disordered blood lipid metabolism, glucose-free dialysate is widely utilized in China and European countries. While glucose-free dialysis does not necessarily lead to hypoglycemia, several other metabolic adjustments must occur to maintain normal blood glucose levels. Additionally, glucose-free dialysis may also increase the loss of amino acids and the susceptibility to hypotension and cardiovascular events. Incorporating an appropriate amount of glucose into the dialysate can help to offset the insufficient blood glucose during hemodialysis (HD), potentially reducing the incidence of hypoglycemia. Currently, the efficacy and safety of glucose-containing dialysate during HD remain contentious, and this study will be conducted to evaluate the efficacy and safety of 5.5 mmol/L glucose-containing dialysate for maintenance HD patients.

**Study design and methods:**

A multicenter, prospective, open-label, parallel-group, randomized controlled trial (RCT) will be conducted at more than 30 dialysis centers in China. Approximately 600 participants undergoing maintenance HD will be enrolled. Eligible patients will be randomly assigned to two groups, receiving either glucose-containing dialysate or glucose-free dialysate for HD at a 1:1 ratio, determined by a central computer-generated randomized sequence. The primary outcome is the incidence of the major cardiovascular and cerebrovascular adverse events (MACCE). Secondary outcomes are all-cause mortality, incidence of intradialytic hypotension (IDH), incidence of hypoglycemia, blood pressure and blood glucose variability, dysfunction of vascular access, cardiac function and fatigue level. Outcome assessors and data analysts will be blinded. All data will be analyzed using either intention-to-treat or per-protocol analysis methods.

**Discussion:**

The results of this study will provide evidence on the efficacy and safety of 5.5 mmol/L glucose-containing dialysate for maintenance HD patients, and will provide valuable insights for future dialysate selection and the enhancement of dialysis treatment prescriptions.

**Trial registration number:**

ChiCTR2400083153.

## 1. Introduction

With the increasing prevalence of diabetes, hypertension and obesity, an increasing number of patients would develop chronic kidney disease (CKD), with a considerable number eventually progressing to end-stage kidney disease (ESKD) and requiring renal replacement therapy [1]. Hemodialysis (HD) is the most common form of renal replacement therapy for patients with ESKD. Currently, dialysate used in most hemodialysis facilities is glucose-free dialysate, which provides advantages such as less risk of infection and disordered blood lipid metabolism [2]. However, as type 2 diabetes (T2DM) has become a leading cause of ESKD, the risk of severe hypoglycemia (<5.55 mmol/L) during HD has become a concern, as it is associated with seizures, stroke, and higher mortality [3,4]. Due to issues such as impairment of renal gluconeogenesis, malnutrition, and the use of glucose-free dialysate, HD patients are more susceptible to hypoglycemia. As high blood flow with continuous flow of glucose-free dialysate or low glucose dialysate through dialyzer, a loss of 20–40 g of glucose would occur during each hemodialysis session, which is an important element in the occurrence of hypoglycemic events during HD [5,6].

Adding an appropriate amount of glucose to the dialysate can help reduce the loss of glucose during HD, and potentially decrease the incidence of hypoglycemia [7]. And currently, several studies have shown benefits of glucose-containing dialysate in preventing asymptomatic hypoglycemia during HD. Dialysate containing 5–10 mmol/L glucose has been found to reduce the incidence of hypoglycemia and hypotension, as well as improve heart rate variability [8,9]. A prospective crossover study conducted by Li et al. showed a reduction of blood glucose with both glucose-free dialysate and dialysate containing 5–10 mmol/L glucose during HD. However, the glucose-containing dialysate had a lower incidence of hypoglycemia and serum sodium level [10]. In addition, several studies also indicated that glucose-containing dialysate could better control blood glucose and reduce glycemic fluctuations in both diabetic and nondiabetic ESKD patients during HD [11,12].

However, some studies have not unanimously identified glucose-containing dialysate as a superior choice for all maintenance HD patients. High level of hepcidin-25 takes part in the pathophysiology of cardiovascular disease in maintenance HD patients. During HD, glucose-containing dialysate would upregulate the synthesis of hepcidin-25 through oxidative stress, and the activation of the sympathetic nervous system [13]. Additionally, a longitudinal interventional study conducted by Ramsauer et al. suggested that the use of glucose-free dialysate might delay the development of cardiovascular disease [14]. In comparison to glucose-containing dialysate, the use of glucose-free dialysate can significantly decrease the level of skin autofluorescence (SAF), which is an indirect risk factor for cardiovascular disease [14].

Currently, the efficacy and safety of glucose-containing dialysate during HD is still controversial. The existing studies are mostly observational in nature, with small sample sizes and a lack of conclusive evidence on the long-term prognosis of maintenance HD patients with glucose-containing dialysate. To address this gap, we designed a multicenter, prospective, open-label, parallel-group, randomized controlled trial to evaluate the efficacy and safety of 5.5 mmol/L glucose-containing dialysate for maintenance HD patients. This trial will evaluate multiple outcomes, including the incidence of major cardiovascular and cerebrovascular adverse events (MACCE), all-cause mortality, and hypoglycemia, aiming to provide new insights for future dialysis prescriptions and guidelines.

## 2. Methods and analysis

### Study design and setting

The multicenter, randomized controlled trial will be carried out at more than 30 dialysis centers in China (S1 File), comparing the efficacy and safety of glucose-containing and glucose-free dialysate for patients with maintenance HD. This study will be carried out in a prospective, open-label, two-arm, parallel-group design. The study protocol will be designed in accordance with the Standard Protocol Items: Recommendations for Interventional Trials Checklist (SPIRIT) [15] (SIPRIT checklist was shown in S2 File), and the conduct of this study will adhere to the Declaration of Helsinki (version Fortaleza, 2013). And the original protocol approved by the ethics committee was shown in S3 File. The enrollment schedule and the flowchart of the trial procedure are summarized in **Fig 1 and Fig 2**.

**Fig 1 pone.0330155.g001:**
[figure not shown]
The schedule of enrollment, interventions, and assessments. *Routine blood biochemical examination includes liver function (ALT, AST, ALP, Alb, TB and DB), renal function (SCr and BUN), electrolytes (blood calcium and phosphorus), blood lipids (TC, TG, LDL and HDL).

**Fig 2 pone.0330155.g002:**
[figure not shown]
The summarized design of this trial. MACCE: major cardiovascular and cerebrovascular adverse event; IDH: intradialytic hypotension.

### Ethical approval and study registration

This study was approved by the biomedical research ethics committee, West China Hospital of Sichuan University in China (2023. 2248), and was registered with the China Clinical Trial Registry (ChiCTR2400083153).

### Participants

All patients requiring maintenance HD will be assessed for eligibility. Both diabetic and non-diabetic patients will be included in the study. Details regarding diabetes pharmacotherapy, including oral hypoglycemic agents and insulin regimens, will be systematically documented. The inclusion criteria are as follows: (1) Age between 18 and 75 years; (2) Having undergoing maintenance HD three times a week for at least three months and the dialysis modality has remained stable; (3) Kt/v ≥ 1.2 in the last 8 weeks before entering the study; (4) Provision of informed consent prior to any study specific procedures. And the exclusion criteria include: (1) Participants with life expectancy less than 1 year; (2) Participants hospitalized due to decompensation or any other complications of diabetes within 3 months; (3) Participants under active infection or active cancer treatment; (4) Receiving glucose-containing dialysates in the past 3 months or intolerance to glucose-containing dialysates; (5) Planned coronary intervention, or cardiac treatment (e.g., valve); (6) Participation in another clinical intervention trial within the last 3 months; (7) Pregnancy, or impending miscarriage; and (8) Inability of the patient to understand or comply with the study.

Eligible patients will be informed clearly of the objective, procedure, expected benefits, and possible risks involved. Both the patient and treating physicians are required to complete and sign the informed consent form. Confidentiality of all patient information will be maintained, and patients have the right to withdraw from the study at any time without facing any prejudice.

### Randomization and blinding

After obtaining the written informed consent (S4 File), eligible patients will be randomized in a 1:1 ratio to receive either glucose-containing or glucose-free hemodialysis dialysate, with allocation determined by a centrally computer-generated randomization sequence. To ensure balance between groups, we will implement stratified block randomization using diabetic kidney disease (DKD) status as the stratification factor. Participants will be categorized into DKD and non-DKD subgroups, with each stratum undergoing separate randomization using computer-generated sequences with randomly permuted block sizes of 4 or 6 to maintain the 1:1 allocation ratio while preventing predictability in treatment assignment. Group A will receive glucose-containing dialysate for HD, and group B will receive glucose-free dialysate. Due to practical considerations, blinding of patients and treating clinicians was clinically impractical during this study. But the outcome assessors and data analysts will be fully blinded throughout the study to minimize bias.

### Intervention and comparison

Patients will be randomly allocated into two groups. Group A will receive glucose-containing dialysate for HD (dialysate flow rate 500 ml/min, sodium 138 mmol/L, potassium 2.0 mmol/L, calcium 1.25–1.75 mmol/L, bicarbonate 33.5 mmol/L, glucose 5.5 mmol/L, temperature 35.5−37 °C, bacterial count<100 cfu/ml, endotoxin<0.5 EU/ml). And group B will receive conventional glucose-free dialysate for HD (dialysate flow rate 500 ml/min, sodium 138 mmol/L, potassium 2.0 mmol/L, calcium 1.25–1.75 mmol/L, bicarbonate 33.5 mmol/L, temperature 35.5−37 °C, bacterial count<100 cfu/ml, endotoxin<0.5 EU/ml). Both groups will receive the same dialysis prescription: maintenance HD three times per week; arteriovenous fistula (AVF), tunnel-cuffed catheter (TCC) or arteriovenous graft (AVG) as vascular access; dialysis fluid flow rate of 500 ml/min; blood flow rate of 200–300 ml/min; Prioritize using of high cutoff dialyzer with a membrane area of 1.4−1.8m^2^ and a membrane ultrafiltration coefficient over 20 ml/h/mmHg; Unfractionated heparin (UFH) or low-molecular-weight heparin (LMWH) as anticoagulants.

### Primary outcome

The primary outcome will measure the incidence of the major cardiovascular and cerebrovascular adverse events (MACCE). MACCE is defined when the following conditions occur during maintenance HD: (1) Occurrence or deterioration of congestive heart failure and myocardial infarction; (2) Cardiogenic shock and/or sudden cardiac death; (3) Transient ischemic attack or occurrence and deterioration of Cerebral infarction and cerebral hemorrhage; (4) Pulmonary embolism and peripheral arterial thrombosis or embolism [16].

### Secondary outcomes

The secondary outcomes include:

(1)All-cause mortality at 1year, 2 years and 3 years follow-ups.(2)The incidence of intradialytic hypotension (IDH). According to the National Kidney Foundation Kidney Disease Outcomes Quality Initiative (KDOQI), IDH is defined as “a decrease in systolic blood pressure (SBP) by ≥ 20 mmHg or a decrease in mean arterial pressure (MAP) by ≥10 mmHg, accompanied by hypotension symptoms such as abdominal discomfort, yawning, sighing, nausea, vomiting muscle cramps, restlessness, dizziness or fainting, and anxiety” [17]. In addition, we will compile the proportion of patients with an absolute nadir systolic BP < 90 mmHg (pre-dialysis systolic BP < 160 mmHg) or a nadir BP < 100 mmHg (pre-dialysis BP ≥ 160 mmHg) during HD, as it most potently associated with mortality [18].(3)The incidence of hypoglycemia. A serum glucose level below 3.9 mmol/L (70 mg/dl) is defined as hypoglycemia [19,20]. In addition, three levels of hypoglycemia will be classified according to the American Diabetes Association [21, 22]. Level 1 hypoglycemia: a serum glucose concentration <3.9 mmol/L) but ≥3.0 mmol/L, regardless of hypoglycemia symptoms, including but are not limited to, shakiness, irritability, confusion, tachycardia, sweating, and hunger. Level 2 hypoglycemia: a serum glucose concentration <3.0 mmol/L. Level 3 hypoglycemia: a severe hypoglycemia event (altered mental and/or physical functioning) that requires assistance from another person for recovery, irrespective of glucose level.(4)Blood pressure variability during HD. Systolic blood pressure (SBP) and diastolic blood pressure (DBP) will be measured before HD, every hour during HD, and after HD. Blood pressure coefficient of variation (CVBP) will be used to represent the variability of SBP and DBP during HD. CVBP = standard deviation of blood pressure/ mean blood pressure.(5)Blood glucose variability during HD. Within the first 48 weeks after enrollment, we will measure blood glucose (postprandial blood glucose) during the first HD process each week (0h before HD, 2h during HD and 0h after HD). Blood glucose coefficient of variation (CVBG) = standard deviation of blood glucose/ mean blood glucose.(6)Dysfunction of vascular access.(7)Cardiac function. Left ventricular end diastolic diameter (LVEDD), left ventricular posterior wall thickness (PWTd), interventricular septal thickness (SWTd), and left ventricular ejection fraction (LVEF) will be measured using echocardiography. Meanwhile, we will also calculate relative wall thickness (RWT), left ventricular mass (LVM), and left ventricular mass index (LVMI).(8)Fatigue level: ICFS-10 fatigue rating scale and the 9-item Fatigue Severity Scale (FSS) [23].

### Patient safety

Any adverse events occurring during HD, including metabolic complications (hypoglycemia, hyperglycemia) and cardiovascular events (hypotension, hypertension and arrhythmia), will be actively monitored and documented throughout the study period. Any adverse event will be fully recorded, including the time, severity, and process description of adverse events, measures taken, and the causal relationship assessment between adverse events and treatment.

### Data collection and management

All researchers will attend a training course of participants enrollment, outcomes assessments and data collection before starting the study. All data will be recorded in detail on the electronic data capture (EDC) system accurately, timely, standardly and completely. And the chart for data collection and management was detailed in **Fig 3**.

**Fig 3 pone.0330155.g003:**
[figure not shown]
Chart for data collection and management. CRC: Clinical research coordinator; Sub-I: Sub-investigator; PI: Principal investigator; CRA: Clinical research associate; EDC: Electronic data capture; DM: Data management; DB designer: Database designer; ME: Medical expert.

### Sample size determination

Sample size calculation was performed based on the primary outcome MACCE. Our hypothesis posits that the risk of MACCE in the glucose-containing dialysate group will decrease by 25% compared to the glucose-free dialysate group. The Log-rank test was used to compare the primary outcome between groups. We anticipate completing the enrollment within 1 year, and followed by a 3-year follow-up period. We performed sample size calculations with PASS 15.0.5 utilizing an α value of 0.05 and a power of 90%. Accordingly, we require a total of 544 participants (272 per group). Taking into account a potential 10% dropout rate, we determined that 600 participants should be enrolled in this study.

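### The stated 90% power with 544 patients holds only at a very high MACCE rate that the sample-size section does not give

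*Protocol article*

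**What the plan says.** All of the sizing is in the Sample size determination section of the protocol article.

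- Endpoint and test: "Sample size calculation was performed based on the primary outcome MACCE", and "The Log-rank test was used to compare the primary outcome between groups".
- Effect: "the risk of MACCE in the glucose-containing dialysate group will decrease by 25% compared to the glucose-free dialysate group".
- Error rates: "utilizing an α value of 0.05 and a power of 90" per cent. Sidedness is not given.
- Timing: "We anticipate completing the enrollment within 1 year, and followed by a 3-year follow-up period".
- Result: "Accordingly, we require a total of 544 participants (272 per group"), and then "Taking into account a potential 10% dropout rate, we determined that 600 participants should be enrolled in this study".

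Under Randomization and blinding, "eligible patients will be randomized in a 1:1 ratio". No section of the article gives a MACCE rate for either arm or a target number of events.

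**The concern.** The power of a log-rank test is set by the number of events and the hazard ratio. The number of patients matters only through the events they supply. The article prints a power and a patient count but not the event rate that links them, and its 25% can be read on two scales that need very different event numbers. The 90% is nonetheless stated without any condition.

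MACCE is the primary outcome, and the Discussion says the results should support dialysis prescriptions and guidelines. If the true event rate is below the one behind the calculation, a null result would be read as coming from a trial with 90% power when the actual power was lower.

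**Working it through.** **Inputs from the article:** 25% reduction, log-rank test, α = 0.05, power 90%, 1:1 allocation, 1 year of enrolment then 3 years of follow-up, 544 patients, 10% dropout, 600 enrolled.

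**Assumptions of this check:** two-sided test as base case, one-sided also tried; exponential event times. Where a range is given, one end is exactly 3 years of follow-up for everyone and the other is uniform entry over 1 year followed by 3 more years. Control risks are assumed throughout.

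**1. The plan's own figure.** 544 cannot be computed forward, because the control event rate is missing. The rate that would produce it can be solved for.

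**2. If 25% is a hazard reduction (HR 0.75).**
- Events (Schoenfeld) = 4(z₀.₉₇₅ + z₀.₉₀)² / (ln HR)² = 4(1.960 + 1.2816)² / (ln 0.75)² = 507.8, so 508. Freedman's formula gives 515.
- 508/544 = 93%; 508/600 = 85%.
- The control hazard would have to be about 0.92-1.06 per year, which means 60-65% of controls have a MACCE in year 1.
- If all 544 patients had an event, power would be Φ(√(544/4) × 0.2877 − 1.960) = 91.8%, barely above the stated figure.

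**3. If 25% is a reduction in 3-year cumulative risk (risk ratio 0.75).**
- With control risk p, HR = ln(1 − 0.75p) / ln(1 − p).
- With fixed 3-year follow-up, N = events / mean event probability, and N = 544 at p = 0.542. The treated risk is then 0.407, HR = ln(0.593)/ln(0.458) = 0.668, events = 258.2, and 258.2/0.4746 = 544.
- With staggered entry, N = 544 at p = 0.514, HR 0.675.
- So 544 corresponds to a control 3-year risk of about 51-54% and an HR of about 0.67.

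**4. One-sided 5%.** HR 0.75 needs 414 events, and 414/544 = 76%. Risk ratio 0.75 gives 544 at a control risk of about 46-49%.

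**5. An absolute 25-point reduction** would need only about 109-171 patients, so it does not explain 544.

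**6. Power at N = 544, two-sided,** from Φ(√(E/4) × |ln HR| − 1.960), where E is the expected number of events:

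| Assumed control 3-year risk | Risk ratio 0.75 | HR 0.75 |
|---|---|---|
| 30% | 52-57% | 41-46% |
| 40% | 70-75% | 52-57% |
| 50% | 85-89% | 62-66% |

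Counting all 600 enrolled as fully followed adds about 3-4 points.

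**7. Dropout step.** 544/0.9 = 604.4, so 605 would be needed. 600 × 0.9 = 540, which is 4 short of the plan's own 544. (544 × 1.1 = 598.4, which may be how 600 arose.) Where 544 gives exactly 90%, 540 gives Φ(3.2416 × √(540/544) − 1.960) = 89.8%.

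**The case against.** The strongest reply is that no arithmetic error in 544 has been shown. The article speaks of risk and never mentions a hazard ratio. On that plain reading 544 follows from a control 3-year risk a little above one half. The definition under Primary outcome is broad: new or worsening heart failure, myocardial infarction, cardiogenic shock, sudden cardiac death, transient ischaemic attack, stroke, pulmonary embolism, and peripheral arterial thrombosis or embolism. Nothing in the article shows that such a rate is unrealistic. This stands. A reader might infer that 544 is a miscalculation, or that an HR near 0.67 contradicts the stated 25%. Neither follows, because the article never calls 0.75 a hazard ratio.

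A reader might also argue that excluding patients with a life expectancy under 1 year rules out so high a rate. That criterion concerns mortality and says little about non-fatal events such as worsening heart failure.

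Sidedness is open as well. Saying that more than half of controls must have an event is true only for a two-sided test; one-sided, the figure falls just below half. Two-sided is the usual convention, and the one-sided thresholds remain high, so this limits the wording but does not remove the point.

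Finally, this is a condensed article. The ethics-approved protocol is cited as a supplementary file that is not shown, and the missing rate may be there. The omission alone would therefore be a weak point. What remains is that the article prints an effect, a power and a sample size as a finished result, and they agree only under a condition it does not mention.

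**Conclusion.** The concern holds as a statement about conditional power. The 90% is valid only if about 93% of 544 patients have an event (HR 0.75), or if about 51-54% of controls do within 3 years (risk ratio 0.75). One-sided, these become 76% of patients, or 46-49% of controls. On the hazard-ratio reading the stated effect, power and sample size are barely compatible; on the risk-ratio reading they are compatible at one high control rate.

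It would go too far to say that the trial has only about 50% power. The lower figures in the table depend on control risks chosen for illustration, and the article gives no rate against which to judge them. They show how far the headline power moves with the unstated input, not what the power is.

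The dropout slip is real but minor. It costs well under half a percentage point of power and adds no weight to the main point.

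**What to change.** In Sample size determination, replace the unconditional 90% with:

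1. the scale of the 25% (hazard or 3-year cumulative risk) and the sidedness of the test;
2. the number of events required on that scale, for example about 508 for HR 0.75, two-sided;
3. the power, or the detectable hazard ratio, that 600 enrolled patients (about 540 evaluable) give over a range of control 3-year risks, with the assumed control rate identified. The table in the working can serve as a template: moving from 544 to 540 lowers its entries by less than half a point. The HR detectable with 90% power is about 0.57-0.59 at a 30% control risk and 0.62-0.64 at 40%, allowing for the fall in events under a larger effect.

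Restate the evaluable number as 540, or note that 605 would have to be enrolled to keep 544.

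This is a change of wording and requires no extra patients. The cost is a stated power that is less favourable and tied to an event count.
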